### Treatment of Sexually Transmitted Infections

All women diagnosed with symptoms of STIs at any treatment contact will be treated according to PNG Standard Treatment Guidelines for Syndromic Management of STIs, irrespective to treatment allocation.

At enrolment all women will have blood taken to test for syphilis by RPR and TPHA test, and women with positive tests indicating active or latent syphilis will be treated with benzathine penicillin according to standard treatment guidelines.

Self-collected high vaginal swabs will be sent for molecular diagnosis of STIs at the IMR in Goroka. Positive test results will be communicated to the participating women by specially trained staff that will provide counselling to women (and their partners). Women in the control group (as well as partners of all women) will receive treatment according to PNG Standard Treatment Guidelines for Syndromic Management of STIs. As azithromycin in dose given is highly effective in treating all bacterial STIs, women in the intervention group will only receive additional treatment if they are positive for trichomonas.

Consenting women will also undergo testing for HIV (provided routinely by Modilon Hospital), and infected women will be referred to a local treatment centre providing highly active antiretroviral therapy, for prevention of mother to child transmission, and to maintain health of infected women.

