At other regular antenatal care visits women will not be actively followed for morbidity. However, women self reporting febrile illness will be immediately diagnosed by study staff and if required treated for malaria.

At the time of scheduled final treatment dose, women will have a high vaginal swab collected, and all women with symptoms of STIs (or a positive diagnosis by PCR) will be treated according to PNG Standard Treatment Guidelines for Syndromic Management of STIs.

During the entire study period a passive case detection system will be maintained at the participating hospital and health centres (HC) to determine the incidence of symptomatic malaria illness. Every participating woman who presents with a febrile illness or symptomatic anaemia will be clinically assessed and have venous blood (5 ml) taken for the determination of malaria infection (by Rapid Test, confirmed by microscopy and PCR) and Hb level.

The use of a relatively broad spectrum antibiotic for the prevention of malaria and STIs in pregnancy, raises the concern that this intervention my increase resistance in other important bacterial pathogens. Even though the dose given is significantly higher than that recommended for treatment of bacterial illnesses, we will be monitoring resistance level in pneumococci collect from nasal mucosa of a subset of women delivery. Pneumococci were selected as carriage rates are high, and they are easily collected and cultured.

Each participant will thus have up to 4 regular study contacts during gestation and 2 after delivery (6 weeks and 12 months) and will be asked to contribute 2 x 10 ml venous blood samples and 1 or 2 finger prick blood samples (250µl) (See Study Schedule, Appendix I). Additional blood samples will be collected at time of febrile illness during passive case detection.

The safety of all study participants will be assured by a specifically constituted data & safety monitoring board (DSMB), while the study integrity will be guaranteed by regular visits by an external clinical monitor.

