The study team Physician or a trained study team Nursing Officer will assess the woman for sign of chronic illness, symptomatic severe anaemia or permanent disabilities that would preclude her participation into the study. (See 5.2 for list of exclusion criteria). If a woman is excluded on health grounds, she will be referred to nearest health facility for treatment.

Every enrolled woman’s health (record) booklet (already owned, or provided at enrolment) will be clearly marked with a study identifier and study ID number. At any study contact, the study team will record all medically relevant data collected during their examination into the health booklet.

Digital photographs will be taken of participating women at enrolment, and a printed version will be kept in a secure file, for tracking of pregnant women who fail to attend appointments, and to ensure accurate identification of women if required

Following assessment the woman will receive the 1st IPTp treatment dose. The drugs will be dispensed in pre-randomised and pre-numbered Ziploc bags that contain all drugs for initial treatment. The first dose (SP and AZ or SP and chloroquine) will be dispensed directly by the study staff. Pack number, date and time of administration will be recorded on the enrolment forms. The tablets will be administered with water. The woman will then be instructed how to take subsequent AZ or chloroquine doses at home. The woman’s treatment allocation will be noted using randomly-generated codes. Treatment allocation will not be revealed to laboratory staff, and will be kept concealed to the maximum extent possible from other study staff (see 6.3.3.). Senior study investigators will be aware of treatment allocation; hence the study will be single blinded.

A thorough physical examination (including axillary temperature, measurement of Hb etc. will only be conducted on enrolled women who spontaneously report as ill to either the study team or the health centre staff. Women with a presumptive diagnosis of malaria will be tested on the spot for malaria infection using a rapid diagnostic test (RDT). If they have a positive RDT they will be treated with a full course of Coartem and their randomised IPTp treatment (drug or placebo) will be delayed for at least 4 weeks. For all women reported sick, detailed symptomatology, results of RDT and treatments given will be recorded on the ‘Morbidity Surveillance Form’.

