At the end of the enrolment visit the study team will schedule the next treatment visit with the woman. Participants will be instructed to seek medical attention immediately if they have any sign or symptoms of illness or any other condition that they deem as a threat to their well-being following the treatment. They will also be encouraged to seek medical care if they note any symptoms of malaria, fever, or illness, and to report any antimalarial treatments received or used.

1. 2nd Treatment Visit

During the 2nd treatment visit the PNGIMR study team will conduct the following tasks:

Woman:

- Interview and record
  - history of bednet use in two weeks prior
  - history of malaria treatment in two weeks prior
- Take growth measurements
  - Maternal weight
  - Fundal height
- Collect 250 µl finger prick blood sample
  - Prepare thin and thick blood smears
  - Archive a portion of the blood sample for laboratory analyses
- Check the woman’s health records booklet for recent health centre visits and record applicable information
- Measure maternal blood pressure and check for oedema. If elevated blood pressure or oedema present, women will be tested for proteinuria. Presence of all three will be considered clinical evidence of pre-eclampsia, and women will be referred for obstetric care through Modilon Hospital.
- If possible, perform second ultrasound examination for fetal growth monitoring.

Data and responses of the participant will be recorded on the 2nd Treatment Visit CRF at the time the measurements and interview are conducted. As at enrolment a thorough physical examination (including axillary temperature, measurement of Hb, etc.) will only be conducted on enrolled women who spontaneously report as ill to either the study team or the health centre staff conducting the clinic. Women diagnosed with presumptive malaria will be tested on the spot for malaria infections using a rapid diagnostic test (RDT). If the RDT is positive, they will be treated with a full course of Coartem instead of the scheduled treatment. For all women reported sick, detailed symptomatology, result of RDT and treatments given will be recorded on the ‘Morbidity Surveillance Form’.

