Following the collection of data and blood sample women receiving SP + AZ will receive the 2nd IPTp treatment dose, women in the control arm will receive SP and AZ placebos. The first dose will be dispensed directly by the study staff. Pack number, date and time of administration will be recorded on the enrolment forms. The participant will then be instructed how to take the 2nd dose at home.

At the end of the visit the field study team will schedule the next treatment visit with the woman. Women who failed to attend the study ANC clinic will be contacted by the village reporters and encouraged to present at their health centre to receive the missed treatment.

1. Third IPTp Treatment Visit

During the final treatment visit the PNGIMR field study team will conduct the following tasks:

Woman:

- Interview and record
  - history of bednet use in two weeks prior
  - history of malaria treatment in two weeks prior
- Take growth measurements
  - Maternal weight
  - Fundal height
- Collect 250 µl finger prick blood sample (in first 150 women, collect instead 5 ml venous sample for plasma separation and immunological studies).
  - Prepare thin and thick blood smears
  - Archive a portion of the blood sample for laboratory analyses
- Where possible, collect a self-administered high vaginal swab for determination of sexually transmitted infections (STIs)
- Check the woman’s health records booklet for recent health centre visits and record applicable information
- Measure maternal blood pressure and check for oedema. If elevated blood pressure or oedema present, women will be tested for proteinuria. Presence of all three will be considered clinical evidence of pre-eclampsia, and women will be referred for obstetric care through Modilon Hospital.
- Ultrasound will be performed where available to (a) measure fetal growth using bi-parietal diameter, head circumference, abdominal circumference and femur length and (b) document uteroplacental blood flow patterns using color Doppler, as described

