Data and responses of the participant will be recorded on the Final Treatment Visit CRF at the time the measurements and interview are conducted. As at enrolment a thorough physical examination (including axillary temperature, measurement of Hb, etc.) will only be conducted on enrolled women who spontaneously report as ill to either the study team or the health centre staff conducting the clinic. Women diagnosed with presumptive malaria will be tested on the spot for malaria infections using a rapid diagnostic test (RDT). If the RDT is positive, they will be treated according to PNG standard treatment guidelines with a full course of Coartem instead of the scheduled treatment. For all women reported sick, detailed symptomatology, result of RDT and treatments given will be recorded on the ‘Morbidity Surveillance Form’.

Following the collection of data and blood sample the woman will receive the Final IPTp treatment dose (if she is allocated to the SP and azithro arm of the study, or matching SP and Az placebo). Administration will be as for the second treatment dose.

At the end of the visit the field study team will remind the woman of the importance of delivering in the Health Centre or Hospital. Women who fail to attend the study ANC clinic will be contacted by the village reporters and encouraged to present at their local health centre to receive the missed treatment.

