# Study Schedule

**Table 2: Summary of scheduled study activities**

|  |  |  |  |
| --- | --- | --- | --- |
|  |  | **Time** | **Activities** |
|  |  |  |  |
|  |  |  |  |
| **Enrolment Visit** |  | 1st antenatal care visit at < 14 -20 weeks of gestation | - Identification of eligible mother - Enrolment - Baseline Data collection - Collection of venous blood sample - Collection of vaginal swab - Ultra Sounds examination - 1st IPTp treatment |
|  |  |  |  |
| **2nd Treatment Visit** |  | At 22-26 weeks of gestation | - 2nd IPTp treatment - Finger prick blood sample - Collection of data on net use, health seeking, etc - Collection of vaginal swab - Treatment for STIs |
|  |  |  |  |
| **3rd Treatment Visit** |  | At 28-32 weeks of gestation | - 3rd IPTp treatment - Finger prick blood sample - Collection of data on net use, health seeking, etc |
|  |  |  |  |
| **Delivery** |  | At delivery | - Health assessment of mother & child - Measurement of child’s birth weight, & maternal Hb - Collection venous blood & placental blood sample and placental specimen from mother - Cord blood collection from child |
|  |  |  |  |
| **6 Weeks Follow-up** |  | 6 weeks after delivery | - Health assessment of mother & child - Collection of heel prick blood sample from child |
| **3 months follow up** |  | 3 months post delivery (250 consecutive women) | - Health assessment of mother & child - Collection of venous blood from mother |
|  |  |  |  |
| **1 year Follow-up** |  | 1 year after delivery | - Health assessment of child |
|  |  |  |  |

A graphic representation of study activities is given in Appendix I.

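### The rule withholding extra STI treatment from SP/AZ women has no exception when trial azithromycin is deferred or replaced by Coartem, and it conflicts with the Study Design rule for the final-dose swab

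*Combined protocol and SAP*

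**What the plan says.** Section 6.1.8 (Treatment of Sexually Transmitted Infections) treats symptomatic women by national guidelines in both arms, and treats syphilis found at enrolment with penicillin. For infections found by swab PCR it separates the arms:

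- Controls and partners: "Women in the control group (as well as partners of all women) will receive treatment according to PNG Standard Treatment Guidelines".
- SP/AZ arm: "women in the intervention group will only receive additional treatment if they are positive for trichomonas". The reason given is that the azithromycin dose in the trial is highly effective against bacterial STIs.

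Section 6.1.4 (Enrolment and Treatment) describes when that azithromycin is not given on schedule. If a woman is ill with presumed malaria and her RDT is positive, she receives Coartem, and:

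- at the first treatment visit, "their randomised IPTp treatment (drug or placebo) will be delayed for at least 4 weeks";
- at the second, "they will be treated with a full course of Coartem instead of the scheduled treatment";
- at the third, "they will be treated according to PNG standard treatment guidelines with a full course of Coartem instead of the scheduled treatment".

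The Study Design section has a rule of its own for the scheduled final dose, not limited by arm: "all women with symptoms of STIs (or a positive diagnosis by PCR) will be treated according to PNG Standard Treatment Guidelines".

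The documents place the later swab differently. Study Design and the third-visit list in 6.1.4 put it at the final treatment visit. Table 2 puts it at the second, with the entry "Collection of vaginal swab - Treatment for STIs".

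**The concern.** The rule in 6.1.8 is sensible as long as its premise holds: an SP/AZ woman with gonorrhoea or chlamydia is about to take, or has just taken, a course that cures it. When the course is deferred or replaced, the premise fails but the instruction remains. Read literally, she has a diagnosed, treatable infection and gets nothing for it when the result comes back. Her partner, and a control woman with the same result, are treated. The Background section links these infections to prematurity, low birth weight and neonatal disease.

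At the final-dose visit the two rules give opposite instructions for the same asymptomatic woman. Staff who follow 6.1.8 withhold treatment; staff who follow Study Design give it.

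**Working it through.** **Step 1. Who is affected.** The swab PCR detects *N. gonorrhoeae*, *C. trachomatis* and *T. vaginalis* (11.1.1). Symptomatic women are treated under 6.1.8 in either arm. Trichomonas-positive women receive additional treatment; I count them as covered, which is an assumption. That leaves asymptomatic, trichomonas-negative SP/AZ women positive for gonorrhoea or chlamydia who had no trial azithromycin at or after the swab.

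**Step 2. What happens at each visit.**

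| Swab at | If RDT-positive | Later trial azithromycin due? | 6.1.8 | Study Design |
| --- | --- | --- | --- | --- |
| Enrolment | course deferred at least 4 weeks | yes, the deferred course | no treatment on result | silent |
| Visit 2 (Table 2) | course replaced | yes, third course | no treatment on result | silent; its rule is tied to the final dose |
| Last treatment visit | course replaced | no | no treatment on result | treat |

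In the first two rows the effect is a delay. Its net length is unknown: control women also wait for the PCR result from Goroka, and no turnaround is stated. Only in the third row is no azithromycin scheduled before delivery, and there the two sections disagree.

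**Step 3. Scale, for illustration only.** No figure in the plan counts these women. The nearest input is the Table 3 row on bacterial STI, 30% v 10% with 72 per arm. A two-proportion calculation (two-sided 5%, 80% power) returns 72 with continuity correction and 62 without, so the 10% is read correctly as the SP/AZ planning value.

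Inputs from the documents: 1396 women per arm, or 1396 × 0.8 = 1117 after 20% loss; trichomonas 17.6–20.0%; chlamydia from 19.3%; any bacterial STI up to 35.5%; syphilis from 13.6%. Assumed, not in the documents: 2–10% ill and RDT-positive at a visit; swab coverage 60–100%; 0–50% with STI symptoms; independence of trichomonas, bacterial STI and malaria.

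Formula: women × prevalence × coverage × asymptomatic share × trichomonas-negative share × RDT-positive share.

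- Later swab, low: 1117 × 0.10 × 0.6 × 0.5 × 0.80 = 26.8; × 0.02 = 0.5.
- Later swab, high: 1396 × 0.10 × 1 × 1 × 0.824 = 115.0; × 0.10 = 11.5.
- Enrolment, low (chlamydia with full gonorrhoea overlap): 1396 × 0.193 × 0.6 × 0.5 × 0.80 = 64.7; × 0.02 = 1.3.
- Enrolment, high (0.355 − 0.136 = 0.219, assuming no syphilis co-infection): 1396 × 0.219 × 1 × 1 × 0.824 = 251.9; × 0.10 = 25.2.

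Each percentage point on the RDT-positive share changes the count by 0.3–1.2 women at the later swab and 0.6–2.5 at enrolment.

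A cruder version drops the coverage, symptom and trichomonas factors, assumes 1–10% RDT-positive, and lets gonorrhoea and chlamydia overlap fully or not at all (19.3% to 20.0% + 15.1% = 35.1%). It gives 1396 × 0.193 × 0.01 = 2.7 to 1396 × 0.351 × 0.10 = 49.0 at enrolment, and 1396 × 0.10 × 0.01 = 1.4 to 1396 × 0.10 × 0.10 = 14.0 at the later swab. The counts are small either way, and their range is set by the assumptions.

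**The case against.** The strongest reply is that the one serious case is already covered. Study Design deals with the final-dose visit specifically and treats every PCR-positive woman, so she is missed only if the general sentence in 6.1.8 overrides it. Table 2 also lists STI treatment at visit 2 without an arm limit. The 6.1.8 sentence rests on azithromycin having been given, so applying it to a woman who got Coartem instead is not its natural reading. Study physicians are responsible for adequate care, and unseen SOPs may settle the point. The remaining cases are delays, possibly of zero net length.

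Much of this stands, and it limits the point to a small gap. It does not remove it. 6.1.8 is the dedicated STI section and says only; no text gives Study Design precedence; and results come back after the visit, to staff who need a written rule. An earlier azithromycin course does not answer a later positive swab either: Table 3 itself expects 10% bacterial STI in this arm.

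A reader might infer that SP/AZ women with gonorrhoea or chlamydia are generally left untreated, or untreated for the rest of pregnancy. The documents do not support that. Most are due a 4 g course (1 g twice daily for 2 days) at the swab visit, against a curative dose the Background puts at 2 g or less, and at enrolment the course is deferred, not cancelled. Nor do they support a claim of material bias in the low-birth-weight comparison: the counts are too small and too uncertain.

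A reader might also conclude that the conflict should be settled by making Study Design defer to 6.1.8. That would narrow the only text that protects women at the final visit. Only the first dose is given by staff; the rest of the course is taken at home, so the dispensing record does not show that it was completed.

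**Conclusion.** The point holds in limited form. The 6.1.8 rule depends on trial azithromycin being given, has no exception for the situations in which 6.1.4 defers or replaces it, and contradicts Study Design for the final-dose swab. A small number of women could be affected. The ranges in the working depend on an RDT-positive rate that the documents do not give, on prevalences from non-pregnant women outside Madang, and on a Table 3 planning value that may include syphilis (which would lower the later-swab count). They show order of magnitude only. The practical harm is a delay of unknown net length at enrolment or visit 2, and possible non-treatment before delivery at the last treatment visit if 6.1.8 is followed. This is a participant-care matter that justifies a short amendment; it is not a threat to the trial's main result.

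**What to change.** In 6.1.8, keep the sentence on the intervention group and add at its end:

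> , except that intervention women positive for *N. gonorrhoeae* or *C. trachomatis* who have not received trial azithromycin at or after the swab by the time the result is returned (deferred, replaced by Coartem, or not given) receive guideline treatment when the result is returned.

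Then state in 6.1.8 that the Study Design rule governs for the swab at the final treatment dose. Leave Study Design as it is, and do not make it refer back to 6.1.8. The exception is not tied to a visit number, so it works wherever the later swab is taken.

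Cost:

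- Guideline drugs for a few women not given azithromycin, and a look at the administration record when a positive result is returned. Pack number, date and time are already recorded.
- Some duplicate treatment at the final visit of SP/AZ women who did receive azithromycin. With the later-swab inputs above, if that swab is at the final visit, they would be most of the 27–115 asymptomatic, trichomonas-negative positives.
- No new unblinding, since 6.1.8 already acts on allocation.
- Little effect on the STI endpoint. Extra treatment after the enrolment swab precedes the endpoint swab, but concerns about 1–25 SP/AZ women under the assumptions above and matches what controls receive. Treatment prompted by the endpoint swab comes after it.

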## Laboratory Evaluations

### Laboratory Evaluations/Assays

**6.2.1.1. Analyses to be performed at the PNGIMR Laboratories in Madang**

1. **Diagnosis of Malaria Infection by Blood Smear**

Thick (2) and thin (2) smears will be prepared on each participant in the study at every study visit and on an as needed basis during morbidity surveillance by PNGIMR staff who have extensive experience in field preparation of blood smears. Evaluation of the blood smear is performed by examining a total number of oil immersion fields to include 200 leukocytes, with the assumption that mean leukocyte count is 8000/l blood. Results are expressed as the number of asexual parasites per l blood. These methods will be described in the Field and Laboratory Procedures Manual, to be submitted separately.

1. **Blood Sample Processing**

All finger prick blood samples collected during study visits and morbidity surveillance will be separated into plasma and cells and frozen and stored separately. Blood from venous blood draws will be separated into plasma, WBC and RBC fractions using standard protocols. All fractions will be aliquoted and frozen or cryopreserved as required.

From venous and cord blood samples, peripheral blood mononuclear cells (PBMCs) will be extracted after separation of plasma by centrifugation. Cell pellets will be passed over Percoll and the PBMC layer washed, counted and cryopreserved. They will be stored at -80C before transfer to liquid nitrogen. Plasma and remaining cell pellets will be aliquoted for laboratory studies. Detailed procedures for sample separation, storage are given in the immunology sub-protocol and in the relevant SOPs

Detailed procedures for sample separation, storage are given in the immunology sub-protocol and in the relevant SOPs

1. **Genital & Per-Nasal Swabs**

High vaginal swabs (self-collected by study participants) will be obtained and placed into transport medium. Swabs will be stored at -20C and transferred to the IMR’s Goroka laboratory for processing including DNA extraction (6.2.1.2) and PCR as described in the laboratory sub-protocol

Per-Nasal swaps will soaked in the skim milk glucose glycerol broth and stored away at -200 until transport to Goroka microbiology lab.

1. **Host genetic analyses**

In order to obtain high-quality DNA for genomic analysis, individual samples of maternal and infant blood will be extracted using protocols established by MalariaGEN (a malaria genomics study, currently in progress in Madang).

This DNA will be used for host genotyping including common red cell abnormalities like glycophorin C, south east asian ovalocytosis and alpha thalassemia and other know genetic polymorphisms that may alter the risk of malaria.

Results of genetic testing are for research purposes only and will not be passed on the participants.

